## SCHEMA

Patients must have histologically or cytologically confirmed stage IIIB/IVNSCLC  
 One or two prior lines of chemotherapy  
 Age > 21 years.  
 ECOG performance status <2 (Karnofsky >60%)  
 Life expectancy of greater than 3 months  
 Patients must have normal organ and marrow function

[figure not shown]

PK of Vinorelbine and Erlotinib

| Dose Escalation Schedule (see protocol for details)                        |                                                                  |                                          |            |
|----------------------------------------------------------------------------|------------------------------------------------------------------|------------------------------------------|------------|
|                                                                            | Dose                                                             |                                          | Dose Level |
|                                                                            | Conventional Schedule
Vinorelbine (CSV)                       | Metronomic Schedule
Vinorelbine (MSV) |            |
|                                                                            | Vinorelbine (mg/m^2 on
D1,D8 every 21 days) | Vinorelbine
(mg/week)         |            |
| Erlotinib 100 mg
(start 2 days after vinorelbine
for cycle 1) | 30                                                               | 80                                       | Level -1   |
|                                                                            | 40                                                               | 100                                      | Level 1    |
|                                                                            | 50                                                               | 120                                      | Level 2    |
|                                                                            | 60                                                               | 140                                      | Level 3    |
|                                                                            | 70                                                               | 160                                      | Level 4    |
|                                                                            | 80                                                               | 180                                      | Level 5    |

[figure not shown]

Establish MTD with 100 mg Erlotinib

[figure not shown]

Escalate Erlotinib to 150 mg (if MTD not reached at level 5 of vinorelbine)

|                                                                       |                                                                              |                                                               |  |
|-----------------------------------------------------------------------|------------------------------------------------------------------------------|---------------------------------------------------------------|--|
| Erlotinib 150 mg
(if no DLT at dose level 5
vinorelbine) | DLT not reached at dose
level 5 of vinorelbine
(80 mg/m  ) | DLT not reached at dose
level 5 of vinorelbine
(180 mg) |  |
|-----------------------------------------------------------------------|------------------------------------------------------------------------------|---------------------------------------------------------------|--|

## 1. OBJECTIVES

### 1.1 Primary Objectives

- To determine the Maximum Tolerated Dose (MTD) of conventional schedule oral vinorelbine (CSV) combined with erlotinib in patients with NSCLC.
- To determine the Maximum Tolerated Dose (MTD) of metronomic schedule of oral vinorelbine (MSV) combined with erlotinib in patients with NSCLC.

### 1.2 Secondary Objectives

- To assess for pharmacokinetic interaction of erlotinib on navelbine
- To assess the usefulness of circulating endothelial cells (CECs) and circulating endothelial progenitor cells (CEPs) as surrogate biomarkers to determine optimal anti-angiogenic effect of treatment
- To evaluate the clinical benefit rate (CR+PR+SD) and overall survival

## 2. BACKGROUND

### 2.1 Drugs

#### 2.1.1 Oral Vinorelbine

##### Description

NAVELBINE® ORAL

**Vinorelbine 20 mg and 30 mg soft capsules.**

Vinorelbine tartrate is a semi-synthetic vinca alkaloid with antitumor activity. The chemical name is 3',4'-didehydro-4'-deoxy-C'-norvincaleukoblastine [*R*-(*R*\*,*R*\*)-2,3 dihydroxybutanedioate (1:2)(salt)].

Vinorelbine tartrate has the following structure:

[figure not shown]

CAS No: 125317-39-7

Vinorelbine tartrate is a white to yellow or light brown amorphous powder with the molecular formula  $C_{45}H_{54}N_4O_8 \cdot 2C_4H_6O_6$  and molecular weight of 1079.12. The aqueous solubility is >

1000 mg/mL in distilled water.

NAVELBINE® soft capsules also contains the following excipients: ethanol, water - purified, glycerol, macrogol 400, gelatin, sorbitol, sorbitan, medium-chain triglycerides, phosphatidyl choline, glycerides, hypromellose, propylene glycol, edible printing ink E120, titanium dioxide, iron oxide yellow CI77492 and / or iron oxide red CI77491.

### **Pharmacology**

Vinorelbine is an antineoplastic drug. It is a semi-synthetic member of the vinca alkaloid family that interferes with microtubule assembly. The vinca alkaloids are structurally similar compounds comprised of two multiringed units, vindoline and catharanthine. Unlike other vinca alkaloids, the catharanthine unit is the site of structural modification for vinorelbine. The antitumor activity of vinorelbine is thought to be due primarily to inhibition of mitosis at metaphase through its interaction with tubulin. In intact tectal plates from mouse embryos, vinorelbine, vincristine, and vinblastine inhibited mitotic microtubule formation at the same concentration (2 $\mu$ M), including a blockade of cells at metaphase. Vincristine produced depolymerisation of axonal tubules at 5 $\mu$ M, but vinblastine and vinorelbine did not have this effect until concentrations of 30 $\mu$ M and 40 $\mu$ M respectively. These data suggest relative selectivity of vinorelbine for mitotic microtubules.

### **Pharmacokinetics**

Following oral administration, NAVELBINE® is promptly absorbed and the Tmax is reached within 1.5 to 3 hours with a blood concentration peak (Cmax) of approximately 130 ng/mL after dosing at 80 mg/m^2. The absolute bioavailability is about 40% and simultaneous intake of a low fat standard meal does not modify the area-under the concentration-time curve (AUC). The effect of a high fat meal on absorption has not been studied.

NAVELBINE® Oral 60 and 80 mg/m^2 leads to a comparable AUC to that obtained from 25 and 30 mg/m^2 of the IV formulation respectively. Interindividual variability of the AUC is similar after administration by both the IV and oral routes. There is a proportional increase between the AUC and dose. The mean pharmacokinetic parameters were evaluated in blood. After intravenous administration, the terminal half-life averaged 38 hours. Blood clearance was high, approached liver blood flow and averaged 0.72 L/hr/kg (range: 0.32 - 1.26 L/hr/kg), while steady state volume of distribution was large, averaged 21.2 L/kg (range: 7.5 - 39.7 L/kg), and indicated extensive tissue distribution.

Vinorelbine binds extensively to blood cells and especially platelets (70-80%), but less extensively (about 15%) to plasma proteins. There is a significant uptake of NAVELBINE® in lungs, as assessed by pulmonary surgical biopsies showing up to a 300 fold greater concentration than in serum. NAVELBINE® has not been detected in the central nervous system.

NAVELBINE® is mostly metabolised by the CYP 3A4 isoform of the cytochrome P450. All the metabolites have been identified, and none are active except 4-O-deacetylvinorelbine, which is the main metabolite in blood. No sulfo or glucurono conjugates are observed. Renal elimination is low (<20% of the dose) and consists mostly of the parent compound. Biliary excretion is the predominant elimination route of both metabolites and unchanged NAVELBINE®, which is the main recovered compound. The effect of renal dysfunction on NAVELBINE® disposition has not been assessed, however dose reduction in the presence of renal insufficiency is not indicated with

NAVELBINE® due to its low renal elimination.

Vinorelbine is cleared from the circulation primarily by the liver, and therefore elevated blood concentrations may be expected in patients with hepatic impairment. In a Phase I pharmacokinetic study, 6 subjects with severe hepatic impairment were treated with 20 mg/m^2 intravenously. Plasma concentrations were elevated compared to historical data from patients with normal hepatic function. Vinorelbine is contraindicated in patients with severe hepatic insufficiency. There is limited experience in patients with mild or moderate hepatic impairment, however available data suggests that dose modification is not required. Haematological toxicity should be closely monitored. A strong relationship was demonstrated between AUC and leucocyte or PMN decreases.

### **NAVELBINE® Oral**

Oral vinorelbine has been developed as a line extension of the IV dosage form. Hence the primary objective of the clinical program was to demonstrate bioequivalence between the oral and intravenous formulations on the basis of pharmacokinetic studies. An oral dose of 80 mg/m^2 was demonstrated to correspond to 30 mg/m^2 of the IV formulation and 60 mg/m^2 orally to 25 mg/m^2 given by the IV route. Subsequent phase II studies, were conducted to examine the efficacy and tolerance of oral vinorelbine

### **Indications**

NAVELBINE® is indicated as a single agent or in combination for the treatment of non small cell lung cancer (NSCLC).

### **Contraindications**

Known hypersensitivity to vinorelbine or other vinca alkaloids.

Disease significantly affecting absorption.

Previous significant surgical resection of stomach or small bowel.

Neutrophil counts < 1500 cells/mm^3, or current or recent severe infection due to neutropenia (within 2 weeks).

Pregnancy.

Lactation.

Patients requiring long-term oxygen therapy.

Severe hepatic insufficiency.

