### **General**

Most drug-related adverse events of NAVELBINE® are reversible. If severe adverse events occur, NAVELBINE® should be reduced in dosage or discontinued and appropriate corrective measures taken. Reinstitution of therapy with NAVELBINE® should be carried out with caution and alertness as to possible recurrence of toxicity.

Patients presenting with ischaemic cardiac disease should be carefully monitored (see ADVERSE REACTIONS). Acute shortness of breath and severe bronchospasm have been reported infrequently along with rare cases of interstitial pneumopathy following the administration of NAVELBINE® and other vinca alkaloids, most commonly when the vinca alkaloid was used in combination with mitomycin. These adverse events may require treatment with supplemental oxygen, bronchodilators, and/or corticosteroids, particularly when there is a pre-existing pulmonary dysfunction.

Vinorelbine is contraindicated in patients with severe hepatic insufficiency. There is limited experience in patients with mild or moderate hepatic impairment, however available data suggest that dose modification is not required. Haematological toxicity should be closely monitored. NAVELBINE® should not be given concomitantly with radiotherapy if the treatment field includes the liver. Because of the low level of renal excretion, no dose modification is necessary in patients with renal impairment.

Due to the presence of sorbitol, patients with the rare hereditary problem of fructose intolerance should not take this medicine

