3.1.5 Life expectancy of greater than 3 months

3.1.6 Patients must have normal organ and marrow function as defined below:

- |                             |                                                                                               |
|-----------------------------|-----------------------------------------------------------------------------------------------|
| – leukocytes                | $>3,000/\text{mcL}$                                                                           |
| – absolute neutrophil count | $>1,500/\text{mcL}$                                                                           |
| – platelets                 | $>100,000/\text{mcL}$                                                                         |
| – total bilirubin           | within normal institutional limits                                                            |
| – AST(SGOT)/ALT(SGPT)       | $<2.5 \times$ institutional upper limit of normal                                             |
| – creatinine                | within normal institutional limits                                                            |
| OR                          |                                                                                               |
| – creatinine clearance      | $>60 \text{ mL/min/1.73 m}^2$ for patients with creatinine levels above institutional normal. |

3.1.7 The effects of Oral Vinorelbine on the developing human fetus are unknown. For this reason and because vinca alkaloids as well as other therapeutic agents used in this trial are known to be teratogenic, women of

child-bearing potential and men must agree to use adequate contraception (hormonal or barrier method of birth control; abstinence) prior to study entry and for the duration of study participation. Should a woman become pregnant or suspect she is pregnant while participating in this study, she should inform her treating physician immediately.

- 3.1.8 Ability to understand and the willingness to sign a written informed consent document.

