## 3.2 Exclusion Criteria

- 3.2.1 Patients who have had chemotherapy or radiotherapy within 4 weeks (6 weeks for nitrosoureas or mitomycin C) prior to entering the study or those who have not recovered from adverse events due to agents administered more than 4 weeks earlier.
- 3.2.2 Patients may not be receiving any other investigational agents.
- 3.2.3 Patients who have received previous vinorelbine or oral EGFR tyrosine kinase inhibitors
- 3.2.4 Patients with *progressive* brain metastases should be excluded from this clinical trial because of their poor prognosis and because they often develop progressive neurologic dysfunction that would confound the evaluation of neurologic and other adverse events. *However patients are eligible if they have brain metastases that have been treated with whole brain radiotherapy and are stable and not on corticosteroids.*
- 3.2.5 History of allergic reactions attributed to compounds of similar chemical or biologic composition to Oral Vinorelbine or other agents used in study.
- 3.2.6 Prior and / or concomitant treatment with drugs known to induce or inhibit cytochrome P450 3A4, CYP1A1 & CYP1A2 : phenytoin, carbamazepine, barbiturates, rifampicine, imidazole antifungals (such as ketoconazole, fluconazole, itraconazole, metronidazole), omeprazole and ritonavir *within 1 week of starting protocol treatment.*
- 3.2.7 Significant malabsorption syndrome or disease affecting the gastro-intestinal tract function
- 3.2.8 Uncontrolled intercurrent illness including, but not limited to, ongoing or active infection, symptomatic congestive heart failure, unstable angina pectoris, cardiac arrhythmia, or psychiatric illness/social situations that would limit compliance with study requirements.
- 3.2.9 Pregnancy or breast feeding or women of child-bearing potential not using effective contraception.

3.2.10 HIV-positive patients on combination antiretroviral therapy are ineligible because of the potential for pharmacokinetic interactions with Oral Vinorelbine. In addition, these patients are at increased risk of lethal infections when treated with marrow-suppressive therapy. Appropriate studies will be undertaken in patients receiving combination antiretroviral therapy when indicated.

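### Section 3 does not exclude patients on long-term oxygen, a contraindication to oral vinorelbine listed in the protocol itself; prior stomach or small-bowel resection is only partly covered

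*Protocol*

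**What the plan says.** Section 2.1.1 of the protocol (Contraindications) gives eight contraindications to oral vinorelbine. Two matter most here: "Patients requiring long-term oxygen therapy" and "Previous significant surgical resection of stomach or small bowel". The second has its own line, separate from "Disease significantly affecting absorption".

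Eligibility is set in Section 3. Item 3.1.6 opens with "Patients must have normal organ and marrow function as defined below" and then gives laboratory limits. Item 3.2.7 excludes "Significant malabsorption syndrome or disease affecting the gastro-intestinal tract function". Item 3.2.8 excludes "Uncontrolled intercurrent illness including, but not limited to, ongoing or active infection, symptomatic congestive heart failure, unstable angina pectoris, cardiac arrhythmia", together with psychiatric or social circumstances that would limit compliance. Item 3.1.4 requires ECOG below 2 (Karnofsky above 60%).

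Under Precautions, General, Section 2.1.1 describes infrequent acute shortness of breath and severe bronchospasm with vinca alkaloids, seen most often when mitomycin is given as well, and adds: "These adverse events may require treatment with supplemental oxygen, bronchodilators, and/or corticosteroids, particularly when there is a pre-existing pulmonary dysfunction". The same subsection says that "patients with the rare hereditary problem of fructose intolerance should not take this medicine".

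**The concern.** The drug information and the eligibility criteria in one protocol should agree on who must not receive the study drug. Here a site that screens against Section 3 alone can enrol a patient for whom Section 2.1.1 contraindicates the drug. The population is stage IIIB/IV NSCLC after one or two lines of chemotherapy, where home oxygen is plausible.

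What is at stake is patient safety and internal consistency. Error rates and sample size are not affected. Both study drugs carry respiratory warnings. The one for vinorelbine is quoted above. For erlotinib, Section 2.1.2 (Warnings) reports infrequent but serious interstitial-lung-disease-like events, some fatal, and says most cases in the lung cancer trials had contributing factors such as existing parenchymal or metastatic lung disease. A patient who already depends on oxygen has little reserve for either event.

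**Working it through.** No arithmetic beyond a count applies. The check sets each contraindication in Section 2.1.1 beside Section 3.

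| Contraindication (Section 2.1.1) | Criterion in Section 3 | Covered? |
|---|---|---|
| Hypersensitivity to vinca alkaloids | 3.2.5 | Yes |
| Disease affecting absorption | 3.2.7 | Yes |
| Significant stomach or small-bowel resection | 3.2.7, only if malabsorption or GI disease is present | In part |
| Low neutrophils, or current or recent severe neutropenic infection | 3.1.6 (neutrophil limit), 3.2.8 (active infection), 3.2.1 (washout and recovery) | Yes, approximately |
| Pregnancy | 3.2.9 | Yes |
| Lactation | 3.2.9 | Yes |
| Long-term oxygen therapy | None | No |
| Severe hepatic insufficiency | 3.1.6 (bilirubin, AST/ALT) | Yes |

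Count: 6 carried over + 1 in part + 1 absent = 8.

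The next question is whether another criterion excludes an oxygen-dependent patient indirectly.

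- **3.1.6.** The opening words sound general, but organ function is defined by the list that follows: leukocytes, neutrophils, platelets, bilirubin, AST/ALT, creatinine and creatinine clearance. That is 7 lines, of which 0 are respiratory.
- **3.2.8.** The list of illnesses is open-ended, but the governing condition is that the illness is uncontrolled. A patient stable on home oxygen need not meet it.
- **3.1.4.** Karnofsky above 60% admits Karnofsky 70. Appendix A places that score within ECOG 1 and describes a patient who manages self-care but not normal activity or active work. This is compatible with home oxygen.
- **3.1.5.** Life expectancy above 3 months does not bear directly on oxygen use.
- **Study calendar (Section 10).** No oxygen-saturation or lung-function test is named, so no listed test is designed to flag such a patient.

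The remaining exclusions, through 3.2.14, do not mention oxygen. The numbering runs without a gap, so no item has dropped out of the text.

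For resection, the separate line in Section 2.1.1 means that surgery alone is a contraindication. Under 3.2.7 a patient with a significant resection but no malabsorption and no disease affecting GI function still qualifies.

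Section 3 is in places stricter than the drug information. Item 3.2.14 excludes patients on vitamin K antagonists, where Section 2 asks only for monitoring with warfarin. Item 3.1.6 sets renal limits, although Section 2.1.1 says vinorelbine needs no dose change in renal impairment. Against that background, leaving out an outright contraindication looks like an oversight, and the protocol gives no reason for it.

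**The case against.** The strongest reply is that the contraindication is printed in the same protocol. Section 8 sends the reader to Section 2 for the risks of the agents, and Section 2.1.1 puts dosing under a physician experienced in chemotherapy. Someone who reads the whole document is told not to give the drug to this patient, so the defect is a missing line and not an instruction to treat. This stands in part: many such patients would probably be screened out in practice. But the Section 8 pointer concerns adverse events and risks, not eligibility, and enrolment should not rest on the investigator recalling a list in the background section.

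Second, the respiratory mechanism is modest. The vinca reactions are infrequent and mostly linked to mitomycin. Item 3.2.1 bars mitomycin within 6 weeks of entry, and Section 5.1 bars other anticancer agents during the study. The documents do not explain why long-term oxygen is a contraindication. All of this is fair. The finding rests on the contradiction between the two sections and needs no particular mechanism.

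Third, the number affected is unknown, the residual gap for resection is narrow, fructose intolerance is a precaution about a rare condition, and the count of six includes a near match for recent neutropenic infection. These points are correct and limit the weight of the finding. They do not supply the missing criterion.

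**Conclusion.** The concern holds. One of eight contraindications (long-term oxygen) has no counterpart in Section 3, and one (stomach or small-bowel resection) is covered only where malabsorption or GI disease is present. Criteria followed as written admit patients for whom the protocol's own drug information contraindicates the study drug.

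The size in patients is not estimated, because the documents do not give the share of ECOG 0 to 1 patients on home oxygen. That such patients would present is a judgement about the population. No effect on DLT counts, the MTD or pharmacokinetics is claimed: Section 5.2 counts grade 3 or 4 non-haematologic toxicity in cycle 1 but allows attribution to a concurrent medical condition, so the direction of any effect is open. The correction should be made because it is a safety matter and costs little.

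**What to change.** Add to Section 3.2, in order of importance:

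1. Requirement for long-term oxygen therapy. This is the main correction.
2. Previous significant surgical resection of the stomach or small bowel, whether or not malabsorption is present. This closes what 3.2.7 leaves open.
3. Known hereditary fructose intolerance. This is a minor alignment with the precaution in Section 2.1.1.

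The cost is three short lines in an amendment. All can be checked from the medical history and concurrent medications that the study calendar already requires at baseline, so no new test is needed. A few patients become ineligible. For the first two lines these are patients for whom the protocol already lists a contraindication to vinorelbine, and for the third, patients it already says should not take it.
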